**Primary Objectives:**

- Safety - To determine the adverse events rate per foreskin cleaning technique per study arm
- Efficacy - To compare the different odor levels when examine 3 arms of patients undergoing PrePex circumcision with same personal hygiene and with different foreskin hygiene techniques

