## 9.2 Definition of Adverse Event and Their Recording

AE definition: Any unfavorable and unintended sign, symptom or disease temporally associated with the use of a medical treatment and/or procedure regardless of whether it is considered related to the medical treatment/procedure (attribution of unrelated, unlikely, possible, probable, or definite).

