**In this study, all expected side effects and device related or unrelated AE will be recorded in the CRF.**

The nomenclature for AE should be recorded as in the CTCAEv3 and according to the PrePex MC Classification of Adverse Events and Device Hazards.

NOTE – There may be expected procedure side effects which are not considered as Adverse

Events and will not be included in the primary safety analysis, those include:

- - Localized Edema
  - Oozing
  - Clear exudates
  - Slough (indicators: white caramel tissue over the exposed granulating tissue, may appear on day 9)

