## 9.4 Guidelines to Determine the Relationship of an AE to the Study Device

- Definite: The adverse event is clearly related to the investigational treatment.
- Probable: The adverse event is likely related to the investigational treatment.
- Possible: The adverse event may be related to the investigational treatment.
- Unlikely: The adverse event is doubtfully related to the investigation treatment.
- Unrelated: The adverse event is clearly NOT related to the investigational agent(s).

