## 9.5 AE Regulatory Reporting Procedures

- Any clinical study event that is judged to be a device related AE should be recorded on the Case Report Forms (CRFs) AE pages during the course of the study, as detailed in section 9.2 above. The Principal Investigator (PI) (or designee) and/or study coordinator should ensure that this information will be captured during every study subject visit. Any information that is recorded in the CRF must rely on records in the source document. In this study working sheets are allowed as source documents.
- Whenever a study subject has reported **any** device related AE, the study coordinator or PI designee will discuss the event as soon as possible with the PI (if possible while the study subject is there). The PI must evaluate the event.
- If the AE is not serious, the information will be recorded on the appropriate CRF AE Form as instructed above. The AE will be managed medically as appropriate, and will be followed until resolution.
- Any SAE (according to the definitions above), whether or not related to the investigational product, must be reported by the PI or designee simultaneously to the sponsor’s representative, to the Ethical Committee and to the board immediately (within **24 hours** after learning of the event) for accurate and timely recording and reporting by the CRF's SAE Form and managed medically as appropriate, and will be followed until resolution. At intervals per PI discretion, a follow-up CRF SAE Form will be filled and sent to the sponsor's representative. Any relevant information available on the event (hospital records, lab tests, discharge summaries, etc.) will be applied to determine whether the SAE is Unexpected AND related to the investigational product and requires reporting the event to the Ethical Committee and to the MOH ("Expedited Safety Report", see section 9.6 ahead). Any additional information on the SAE should be also forwarded to the sponsor’s representative for further follow-up on special SAE follow-up forms.

Each SAE will be summarized in a form of a "SAE Report".

- **All SAE Reports shall be sent to the Ethics Committee periodically, unless in the following incidences:**

**- Within 48 hours of learning of event occurrence in case of any unexpected** **and device related** **SAE**.

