**Other AEs**

- Liver or pancreatic abnormalities;
- Neurologic conditions of the central nervous system (e.g., meningitis, encephalitis, convulsions and headaches, visual and auditory disturbances, strokes), and peripheral neurologic conditions (e.g., peripheral neuropathies, motor weakness etc.);
- Myocarditis and pericarditis;
- Dermatologic condition affecting the genital, pubic or perianal areas or groin; and,
- Injuries and accidents.

Common illnesses unrelated to male circumcision will not be included in the “other AE” category to avoid unnecessary reporting of irrelevant events. Such AEs include the following:

- Malaria and other common parasitic infections;
- Gastrointestinal (GI) tract diseases, including diarrhea, gastroenteritis (bacterial, viral or parasitic), and other GI conditions, and oropharangeal infections;
- Respiratory illnesses (Upper Respiratory Tract Infections, acute lower respiratory infection, pleurisy), including tuberculosis, influenza or other respiratory infections;
- Angina, myocardial infarction, congestive cardiac failure;
- Dermatologic conditions (e.g., scabies, infected and uninfected rashes, pruritis, fungal infection), except those affecting the genital, pubic or perianal areas or groin
- Neoplasms not affecting the genitourinary tract; and,
- Surgical conditions not related to the intervention (e.g., hernias) and which do not require hospitalization.

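### Section 9.5 ties AE recording and investigator evaluation to device relatedness, against Section 9.2, and Section 9.4 never names the randomised cleaning technique as a causality target

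*Protocol*

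**What the plan says.** **Section 9.2** defines an adverse event by timing, not cause: it counts "regardless of whether it is considered related to the medical treatment/procedure". Its recording rule is equally broad: "all expected side effects and device related or unrelated AE will be recorded in the CRF".

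**Section 9.5** opens with a narrower instruction: "Any clinical study event that is judged to be a device related AE should be recorded on the Case Report Forms". The same sentence then refers back, "as detailed in section 9.2 above". The second bullet makes the investigator's involvement depend on the same condition, namely that the subject has reported a "device related AE, the study coordinator or PI designee will discuss the event as soon as possible with the PI". The third bullet sends non-serious AEs to the AE form in line with the instruction before it. Serious events are handled differently: they are reported whether or not they are related to the product.

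**Section 9.4** is headed "Guidelines to Determine the Relationship of an AE to the Study Device". Under that heading, four of the five categories refer to the investigational treatment and the fifth to investigational agents. Neither term is defined.

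**Objectives.** The second list of primary objectives in the Synopsis gives the safety aim as "To determine the adverse events rate per foreskin cleaning technique per study arm". The first Synopsis list and Section 2 give odor as the sole primary objective, and Section 3 gives odor as the sole primary endpoint. In those places the safety of the cleaning procedure is secondary.

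**The concern.** Whether an event is related to the device is a natural question in a device trial. It is the wrong filter here, because every subject has the standard PrePex procedure. What is randomised is the cleaning: soap in the shower, soapy water by syringe, or chlorhexidine by syringe. A skin reaction to the agent or an abrasion from the syringe may quite properly be judged unrelated to the device. These are also the events by which the arms could differ in safety.

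If such an event is not entered on the AE page, and not brought to the investigator because it fails the device-related condition, no later analysis can recover it. The trial is open label with blinded odor assessors, and nothing in the protocol says that the staff who judge relatedness are blind to arm. The omission could therefore differ between arms.

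**Working it through.** **1. The two recording rules side by side**

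| Item | Section 9.2 | Section 9.5 |
|---|---|---|
| Non-serious AE, device related | in the CRF | on the AE pages |
| Non-serious AE, not device related | in the CRF | not named; only the reference back to 9.2 covers it |
| Investigator discussion and evaluation | not addressed | triggered by a device-related AE |
| Serious AE, any cause | in the CRF | reported whether or not related |

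The rules agree in the first and last rows and part in the second. The cross-reference to 9.2 sits inside the very sentence that carries the condition. It can be read as importing the rule of 9.2, or merely as saying how the named events are to be recorded. The clause on serious events shows that the authors used unrestricted wording in the same section when they meant it.

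The third row is a separate gap. Section 9.2 says nothing about investigator evaluation, so the cross-reference cannot repair that trigger.

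**2. The causality target**

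Section 9.4 names the study device (heading), the investigational treatment (four categories) and investigational agents (last category). If the treatment means the device, a chlorhexidine reaction is unrelated. If it includes the assigned cleaning, the same reaction may be definite. Two assessors can grade one event at opposite ends of the scale and both be following the text. Sections 9.4 to 9.6 nowhere mention the cleaning technique.

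**3. The AE classification**

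The table for the period while the device is worn, which is when the cleaning is done, has rows for pain, displacement, early removal, edema and hematoma. It has none for infection or skin reaction. Genital skin conditions do appear as a reportable class under Other AEs. The list of illnesses not to be reported there includes "Dermatologic conditions (e.g., scabies, infected and uninfected rashes, pruritis, fungal infection), except those affecting the genital, pubic or perianal areas or groin", so local reactions are kept and skin reactions elsewhere on the body are left out.

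**4. Scale**

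The only design figure used is the 33 per arm of Section 8.3. It reproduces for d = 0.7, 80% power and two-sided 5%: n = 2 × (1.96 + 0.842)² / 0.7² = 32.04, rounded up to 33. The t-test solution is 33.02, with power 0.7997 at 33. The point does not rest on this figure; it supplies the denominator.

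- One event: 1/33 = 3.0 percentage points.
- Exact (Clopper-Pearson) 95% intervals at n = 33:

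| Events recorded | Rate | 95% CI |
|---|---|---|
| 0 | 0% | 0% to 10.6% |
| 1 | 3.0% | 0.08% to 15.8% |
| 2 | 6.1% | 0.7% to 20.2% |
| 3 | 9.1% | 1.9% to 24.3% |

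The upper limit for zero events is 1 − 0.025^(1/33) = 0.106. The counts are assumptions that show sensitivity; the protocol gives no expected rate of cleaning-related events. If three occurred in one arm and none was entered, the reported result would move from the last row to the first.

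**The case against.** The strongest reply is that 9.2 is the section on recording, states its rule in bold, and is cited by 9.5, whose own heading concerns regulatory reporting. Nothing gives 9.5 precedence. The schedule of events also calls for side effects and AEs, and for a genital examination, on days 0, 3, 5 and 7 with no relatedness condition. A local reaction, the likeliest kind given where the cleaning is applied, falls in a named class of the AE classification.

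Most of this stands, and it rules out three stronger readings that a reader might infer:

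- **That 9.5 records device-related events and nothing else.** The word *only* is not there, the sentence refers back to 9.2, and serious events are covered regardless of cause.
- **That 9.4 judges causality against the device alone.** That is true of the heading. The scale itself is ambiguous and could include the cleaning.
- **That the per-arm safety result is biased toward no difference.** That needs events to occur, to be judged unrelated to the device, and to be left off the form despite 9.2. Unblinded staff could also over-report in the chlorhexidine arm, so the direction is open.

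Nor can safety per cleaning technique be called primary without qualification, since the lists of objectives disagree.

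What the reply does not remove is the conflict itself: a condition in the site instruction that its source section lacks, an investigator trigger that 9.2 does not reach, and a causality scale with no defined target.

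**Conclusion.** The wording of 9.5 conflicts with that of 9.2, and 9.4 leaves the causality target unclear. In a trial that compares cleaning techniques under a common device, this exposes the per-arm AE rate to loss of non-serious events caused by the agent or the syringe. The safety of the cleaning procedure is an objective in every list, whether primary or secondary, so the point does not depend on which list prevails.

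It is a risk under a literal reading of 9.5, not a prescribed omission. Its frequency and direction are not established; each lost event costs 3.0 percentage points, assuming 33 analysed per arm. It deserves correction because data never recorded cannot be restored in analysis and the change is nearly free.

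**What to change.** - **Section 9.5, first two bullets:** replace the device-related condition with wording that covers any AE, whether or not device related, so that AE-page recording and investigator evaluation match 9.2.
- **Section 9.4:** state that relationship is judged separately to the device and to the assigned cleaning technique (agent or syringe), and use the same terms in the heading and all five categories.
- **Per-arm AE rate:** base it on all recorded AEs, not on those judged device related. The expected side effects that 9.2 sets apart stay as they are.

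The cost is a few sentences of protocol text, one extra field on the AE page, and a small number of additional non-serious events to record and evaluate.

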## 9.6 Serious Unexpected Device Related Adverse Events Reported by the Sponsor (Expedited Safety Reports)

All Serious Unexpected Device Related Adverse Events reports that will be issued by Sponsor will be forwarded as "Expedited Safety Reports" to the PIs. Each PI will send these expedited safety reports to the ETHICS COMMITTEE (the PI in each site should have notify the ETHICS COMMITTEE of such event 48 hours after learning of the event as mentioned above, not in a form of "Expedited Safety Report"). Sponsor will send such reports to the MOH as required the international and national guidelines. The PI and/or study coordinator will file copies of these safety reports in the regulatory binder of the site file.

## 9.7 Clinical Management of Study Related Adverse Events

AEs will be clinically managed according to medical indications, and the standard of care in the specific Medical Center.

Subjects will be entitled for continuation of clinical follow-up and treatment until of their study related clinical problem has been resolved.

## 9.8 Criteria for Study Termination

Termination of the study may be due to any of the following reasons:

- Device related SAEs which are life threatening in at least two cases.
- Device failures in more than 5% of the cases.
- Other ethical or clinical considerations
- Decision by the investigator or sponsor that termination is in the subjects’ best medical interest

# Study Monitoring

## 10.1 Study Records/Source Document Inspection

The investigator will allow the research team (nurses, data managers etc.), representatives of Sponsor, its monitoring team, the MOH of Rwanda, and other governmental regulatory agencies to monitor/audit/inspect all study records, CRFs, IRB/IEC records, and corresponding portions of the subject’s office and/or hospital medical records at regular intervals throughout the study. These monitoring/audits/inspections are conducted to verify adherence to the protocol, integrity of the data being captured on the CRFs and compliance with applicable regulations. Sponsor obliged that subjects’ medical records will be maintained in a confidential manner. Study reports will not identify subjects by name or other identifiers.

## 10.2 Monitors

Each study's site will be monitored by a qualified representative of the Sponsor or any qualified monitor delegated to do so, on behalf of the Sponsor to monitor each study subject’s data and study conduct at regular intervals throughout the course of the study according to a pre-defined monitoring plan. On site monitoring of the investigator’s facilities aids in ensuring compliance with the protocol.

Any deficiency noted during the monitoring visits will be discussed with the investigator and the corrective actions to be taken agreed upon. Should the sponsor determine, at any time during the study that the investigator is not in regulatory and/or protocol compliance, measures necessary to establish compliance will be implemented. If compliance cannot be maintained, the sponsor will suspend or terminate the study at this site.

## 10.3 Monitoring Plan

***I. Pre-Study Visit***

1. Assess the site’s infrastructure (staff and facility) for the capability to conduct the study.
2. Evaluate Investigator and staff’s Experience, Qualifications and Capabilities- signed and dated CVs.
3. Financial Disclosure information.

The sponsor may waive the pre-study visit in certain sites based on previous knowledge or experience with the site or personnel, or other reasons as deemed acceptable.

***II. Study Initiation Visit***

Orients the investigator’s staff involved in the study on

1. Protocol content and procedures
2. CRF and fill-in process including queries resolution process
3. GCP and other regulatory requirements
4. Informed Consent form and process
5. AE, SAE, Safety reporting
6. Ethical Committee
7. Investigational product accountability
8. Subject information- subject’s identification log, subject pre-screening and screening logs, subject enrollment log, subject study visit log
9. Study monitoring
10. Investigator’s site file (ISF)
11. Report of AE back from the Sponsor to the sites (Expedited Safety reports)
12. Expectations from the site regarding data collection and timelines
13. Ministry of health

The sponsor may choose to perform a regional Investigator Meeting instead of the initiation

visits at each site.

***III. Regular Monitoring Visits***

1. Check on the progress of the study
2. Protocol and GCP compliance
3. Informed Consent form and process
4. CRF completion, correction, source data verification
5. AE, SAE, Safety reporting
6. Investigational product
7. Investigator’s study file
8. Pictures and videos

Detailed monitoring schedule to be provided at study initiation

***IV. Final Study Visit - Close Out Monitoring Visit***

Ensure Investigator understands the on-going responsibilities

1. Record archival practices for source documents and CRFs after completion of the study - up to 15 years.
2. Follow-up of on-going device related adverse events - up to 30 days after completion of the study and of SAE – until resolution.
3. Notify the sponsor in the event of Health Authority inspection.
4. Finalizing all "open" issues and complete Source Data Verification (SDV).

# Records handling and Keeping

## 12.1 Source Documents

Source documents are the initial documents whereon subject data are recorded. This includes, but is not limited to, original subject files, hospital records, and original recordings/tracings from automated instruments, etc.

The sponsor allows securing dedicated work sheets to serve as source documents to collect the available source data, on top of all other applicable source documents in the site.

All information captured on the CRF should be accurately supported by the source documents unless specifically approved and documented by Sponsor.

For example, each subject’s source documents should include (but not be limited to):

- Documenting the Informed consent process
- Subject full name and identification
- Date of each study required visit with a description of the visit and the results of each procedure that was performed
- A full and comprehensive anamnesis that will cover subject's medical history, current disease etc.
- All concomitant procedures and medications for the screening eligibility purposes and regular visits

Any additional information relevant to the study should be included in the subject’s source documents. In particular, any deviations from the study protocol or procedures should be recorded in the source documents, if noted. For example, if study required procedures or visits are not completed or are completed outside the time frame specified in the protocol, the reasons for the departure should be explained in the source documents, or mentioned whether it was waived by the Sponsor in advance. The investigator must maintain all study documentation at least 2 years after the last approval of marketing application and until there are no pending or contemplated marketing application or at least 2 years have elapsed since the formal discontinuation of clinical development of the investigational product. These documents should be retained for a longer period, however, if required by the applicable regulatory requirements or by an agreement with the sponsor. The sponsor should inform the investigator in writing when the trial-related records are no longer needed.

## 12.2 Data Collection Method

Data from the subject’s permanent medical records (see source documentation section) will be recorded on CRFs supplied by the sponsor. These CRFs will be used to transmit the information collected in the performance of this study to the clinical database either manually or by site data entry (a third party vendor may be used for this). The CRF for this study will be of standard type with 1 original and a copy will be created, in which the original copy will be kept on site.

Corresponding CRFs should be completed immediately after each subject's visit.

All source data must be typewritten or filled out in ball pens, accurately and promptly following each examination or surgery. The corresponding CRF should be completed that no fields will be left blank. CRFs entries corrections will be made only by crossing out (single line) incorrect data and writing in the revisions. All corrections must be initialed and dated by the individual performing/recording them. If the reason for the change is not obvious, an explanation will be recorded. Blacking out or using correction fluid or an eraser is not allowed to eliminate data. The investigator must review the CRFs for completeness and accuracy and must sign/date the forms where indicated. Signature stamps or substitutes are not acceptable. The investigator will retain originals of all source documents, subject consent forms, and study data as a permanent record.

Each set of CRFs copy should be reviewed for accuracy and completion (signatures, dates, adverse events, serious adverse events, protocol departures) and maintained in the investigator’s study site.

# 13. REGULATORY OBLIGATIONS

## 13.1 Sponsor's Obligations

Clinical research studies are subject to the Rwanda National Ethics Committee approval. A Sponsor must assume the following responsibilities and must keep the required records. He/she must:

1. Provide the Investigator with the necessary information- Protocol and Device User's Manual or Instructions for Use (maybe incorporated to the Investigator Brochure)
2. Inform the Investigator of all new information that may affect his/her decision of whether to continue their participation in the study
3. Provide the supplies (PrePex device and additional materials) for the investigation
4. Provide source to purchase appropriate non-adherent pads for dressing

Maintain the following records:

1. A signed protocol and relevant documents
2. All correspondence that relate to the clinical trial
3. Signed Investigator Agreement
4. Records of device shipment and disposal (shipping receipts, material destruction records, etc.)
5. Other records as required by the Health Authority.

